#### Modifications

We anticipate no substantive modifications of the intervention, since it was piloted and subsequently adapted as part of a preceding feasibility study.

#### Concomitant care

The interventions are planned as an add-on to standard therapy. Prior to the trial, there are no restrictions regarding medication or other finished treatments. In both groups, participants may continue the treatment they received at baseline or start new therapies recommended by their treatment providers. Patients that participate in other intervention studies are however excluded from the study. For more detail, see exclusion criteria. Adjunctive treatment, as well as additional therapies started during the intervention, will be assessed using a self-report questionnaire after completion of therapy and at follow-up.

Additionally, we will instruct patients in both arms to include aerobic exercise in their daily lives, increasing the volume in short intervals of 30–60 s per session and working toward the WHO guidelines on physical activity (150-300 min of moderate-intensity or 75-150 min of vigorous-intensity physical activity per week) [20, 35].

In accordance with the “WHO support sheet for self-management after COVID-19-related-illness”, we will advise participants in both arms to drink plenty of water, wear loose and comfortable clothing and to eat at least one hour before the session. We will also warm-up before and cool-down after training. Regarding breathlessness, we will make sure that the patient can still speak a full sentence without pausing more than once or twice. If he or she cannot do so, we will go back to a lower level of exercise intensity [8].

#### Intervention integrity

We formulated the following core intervention components: 1) individual training sessions supervised by trained health specialists, 2) fixed dose of 2–3 training sessions per week of 30 min each for each patient over a period of approximately six weeks, 3) interventions focus primarily on (Arm 1:) practicing manualized physical activity in immersive virtual reality using the study training device (Icaros flight simulator); or (Arm 2:) practicing manualized physical activity training according to the current standard recommendations of the WHO for treating persistent fatigue after COVID-19 infection and 4) patients following the general instruction to include physical activity in their daily lives as far as possible.

Concerning intervention integrity, we consider criterion 1) to be fulfilled by the fact that all training sessions only take place under face-to-face supervision by a specialist. The two training programmes will be conducted by different personnel in order to maintain blinding and ensure treatment neutrality. Accordingly, specialists in the intervention group and comparison group will be different people who will be assigned their own patients and who will not switch between groups. The respective specialists (persons with a medical-therapeutic background, e.g. medical or psychology students or physiotherapists) will be trained by medical professionals on the respective training programme as well as on medical information about post-COVID, on the difficulties of implementing activation therapy in the treatment of post-COVID and on general issues in the treatment of patients with chronic diseases, and will be regularly supervised (2 × 2 h introductory training, and every 4 weeks—adjust so that it corresponds approximately to the truth). In the intervention arm, this specialist must have completed a training program by representatives of ICAROS ensuring safe and effective handling of the device. In the control arm, this specialist must have a completed training by study coordinates ensuring safe and effective execution of all exercises. Otherwise, the experts will not differ in the extent of their training and the information on the study between the two study arms. In the intervention arm, this specialist must have completed a training program by representatives of ICAROS ensuring safe and effective handling of the device. We consider criterion 2) to be met if a dose of a minimum of ten and a maximum of 18 training sessions (of a minimum of 15 and a maximum of 40 min) has taken place over a period of 4–8 weeks. We will assess the adherence to criterion 3) by requesting therapists in both groups to fill in a self-assessment questionnaire at the end of each training session. This documents the content performed (type of exercises, including intensity, time, and number of repeats with a minimum number of 1 repeat), as well as any deviations from the treatment manual (see additional files 4 and 5). In the intervention arm, patients will additionally fill out the “Igroup Presence Questionnaire” assessing level of immersion [36, 37]. Fidelity is met, if the level of immersion is above “0”. We consider criterion 4) to be met, if patients report in 70% or more session that they remembered to include physical activity in their daily lives since the last session.

For further reference on intervention integrity, please find the fidelity checklist attached as additional file 3. This fidelity-checklist will be used to ensure intervention integrity in both the VR- and the comparison group.

### Outcomes

We will collect patient-reported outcome measures at baseline just prior to randomisation, directly after intervention and at three- and six-months after intervention. These timepoints are frequently applied in RCTs for the treatment of fatigue in chronic conditions and will permit comparisons to be drawn with prior related trials (Heine et al., 2015).

#### Primary outcome

The primary outcome of this trial is the difference in groups in the absolute change in fatigue symptom severity (FSS) score from pre- (T_0_) to post-treatment (T_1_), measured after a standardized 72-h resting state (as defined above). The FSS is a widely used, well-validated clinical rating scale for fatigue symptomatology in chronic conditions [23, 24, 38, 39].

#### Secondary outcomes

Secondary outcomes include the difference in groups in absolute change in FSS score from T_0_ to follow-up at three (T_2_)- and six-months (T_3_) after end of intervention. At T_1_, as well as at T_2_ and T_3_, we will also calculate the absolute change from T_0_ in depressive and anxiety symptom severity (HADS) [40], Post-exertional Malaise (PEM) [41], Post-COVID-scale of functional status [25, 27], Sleep problems with the Jenkins sleep scale (JSS) [42], physical activity with the exercise vital sign [43], pain severity on the MPI-D [44], the Six-minute walk test distance [45] and the hand grip test [46], performance in the concentration and memory tasks, respectively along with burden of specific somatic complaints (Somatic Symptom Disorder–B Criteria Scale, SSD-12) [47, 48] and the Somatic-Symptom-Scale-8 (SSS8) [49], health-related quality of life (SF-12 questionnaire) [50], and EQ-5D 5L [51] and overall impression of change on the patients global impression of change and therapists global impression of change (PGIC, TGIC).

An additional secondary endpoint is the fatigue level responder status at T_1_. Patients with a reduction in fatigue severity of ≥ 15% are classified as responders. This cutoff is consistent with current recommendations for minimal important differences for fatigue patient reported outcome measures [52–54].

### Sample size calculation

Given that this is an explorative trial no formal sample size calculation was performed. However, based on recent data from an intervention study [55] in patients with Post-COVID-associated complaints, in which an FSS post-treatment of 5.0 (SD = 1.4) vs. 3.4 (SD = 1.7) between groups was observed, a mean difference of 0.9 (SD = 1.5) is assumed as a conservative effect considering that no active therapy was offered to the control group in this study. With a sample size of n = 45 per group 80% power is achieved to reject the null hypothesis of equal means assuming a mean difference of 0.9 (SD = 1.5) with a significance level of 5% using a two-sided two-sample t-test. Assuming a drop-out rate of 10%, n = 50 per group will be included. The sample size calculation is based on testing the primary hypothesis that immersive VR-based training therapy leads to a significantly different change in mean fatigue severity score (FSS) from baseline to follow-up assessment (T1) as compared to conventional training therapy in the comparison arm. A difference of 0.45–0.88 points on the FSS is considered clinically relevant [56]; we conservatively define the margin of 0.9 as the minimal clinically relevant difference for our trial. Based on previous post-COVID research [55] we assume a common standard deviation of 1.5 among FSS- fatigue scores.

With a sample size of 45 in the experimental group (immersive neuromuscular training) and 45 in the control group (non-immersive physical activity training), a two-sided test for the difference between two means with a 0.05 significance level has 80% power to detect a difference of 0.9 when the standard deviation is 1.5. Assuming a dropout rate of 10%, we will randomize 100 participants, 50 to each condition.

Sample size calculation was performed in PASS 16.0.12.

### Recruitment

In total, we plan to enrol 100 patients of whom approximately 50% will be allocated to the VR-based immersive neuromuscular training program. To ensure a timely recruitment and to recruit a broad and quite representative sample, recruitment is planned at three different levels (primary, secondary, and tertiary health care). Based on established research cooperations with university teaching practices of primary and secondary care as well as the Long-Covid Network Rhein-Neckar, an interdisciplinary network for the diagnosis and care of patients with Long-COVID complaints, we will be able to start implementation of screening and patient recruitment immediately with ethic approval (Fig. 1).

**Fig. 1 Fig1:**
[figure not shown]
Study flow chart

### Assignment of interventions

#### Allocation

To minimise reporting and selection bias, baseline measures will be collected just prior to randomisation. After giving written informed consent, eligible participants will then be randomly assigned (1:1) to the intervention or comparison arm via a secure web-based randomisation system (Sealed Envelope; https://www.sealedenvelope.com/) operated centrally by a data manager, not involved in the patient recruitment. Central randomisation will ensure concealment of the treatment sequence up to the allocation. The treatment sequence will be a computer-generated sequence of random numbers. Randomisation will be stratified by fatigue symptom severity (stratified by the FSS; three levels: mild, moderate, severe) and age (> 31, 31–50, < 50) using block randomization with variable block length.

#### Masking and patient information

To minimize potential bias due to expectancy and reporting bias, this study is randomized-controlled and blinded in accordance with current recommendations for conducting nonpharmacological trials [22, 57]. By withholding information about the exact content of the interventions and the hypothesis of our study, we attempt to provide the best alternative to a double-blind nonpharmacologic intervention study. Double-blinding encompasses firstly that subjects are not given insight into the content of the control study arm, and secondly that outcome assessors are not informed about what the study objective is and to which intervention arm participants are assigned. All outcome assessors are unaware of all patients group assignments. By also withholding information about the exact content of the interventions and the hypothesis of our study to patients, we attempt to provide the best alternative to a double-blind nonpharmacologic intervention study. Blinding of research staff conducting the intervention to this randomization is not possible. This approach is consistent with current principles for conducting nonpharmacologic intervention studies [58] and is now well established in larger randomized-controlled trials [59].

To minimize differences in expectations between intervention groups, standardized patient education will be provided regarding the exercise programs offered. In addition to the study procedure and the formal conditions of study participation, all participants will be informed in a standardized manner that they will 1.) participate in an individualized neuromuscular training program for the treatment of Post-COVID-associated complaints as part of this study, 2.) be randomly assigned, i.e., by chance, to one of two possible study arms as part of this study and, that 3.) these two study arms are similar in goal, scope, and intensity, but differ in terms of their technical implementation.

In this regard, participants will not receive any information about the specific content of the two treatment groups prior to participation. The patient information leaflet and educational discussion only state that the purpose of the study is to evaluate the effects of neuromuscular exercise therapy on fatigue by comparing two new outpatient exercise programs, without indicating that one of the programs is considered a control intervention (see additional file 6). After randomization, they will be informed about the content of the training program assigned to them via patient information leaflets (see additional files 7 and 8) and will not receive any information about the intervention in the other group. All researchers who assessed the outcomes or performed the data analyses will be masked as to group assignment. Patients will also be instructed not to discuss the content of their training program with other participant during the course of the study and may contact their trainer if they have any problems during study participation. In addition, we will instruct patients before the post-intervention interview not to mention which group, control, or intervention, they belonged to. In the case of unintentional unblinding during the assessment, the assessors will document how, and at which point the unblinding unfolded. Hence, we will be able to subsequently determine the extent to which blinded assessment was successful.

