Core sessions (Session 3–11)	▪ The immersive training programs are conducted under guidance. Participants can always ask questions and receive technical support in setting up the VR set and adjusting the ICAROS system. Before and after each session, the effect of the last session and the current session, respectively, is briefly discussed ▪ Participants can increase the difficulty or the number of ICAROS fights if they stay within their RPE-phase. If training does not lead to worsening of symptoms for at least seven days and patients feel ready to, they can proceed to the next higher exhaustion phase ▪ In those cases, in which an adjustment of the training intensity should become necessary due to subjective exhaustion or Post-exertional malaise, an adjustment of the extent and length is carried out according to the 5-phase model of the WHO recommendations [8]. That means we will return to a lower exhaustion phase ▪ In individual cases where patients arrive to the training session with an initial exhaustion level that is already above their RPE-phase, patients will be asked whether they want to do the training at all. If they want to, repetitions will be performed only on this exhaustion level and no further increase of exhaustion is allowed. In case patients do not feel fit to complete any training, the session will be rescheduled
Closing session (Session 12)	▪ During the last session the subjects are offered to compare themselves with the games from the first session and to reflect on possible changes on a voluntary basis ▪ Short feedback is given and ways to improve the sustainability of the progress made are discussed.

*VR* Virtual Reality*, RPE* subjective rate of perceived exhaustion*, WHO* World Health Organization*, PEM* Post-exertional malaise

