Core sessions (Session 3–11)	▪ The WHO training programs are conducted under guidance. Participants can always ask questions and receive technical support in performing the exercises. Before and after each session, the effect of the last session and the current session, respectively, is briefly discussed ▪ Participants can increase the difficulty or the number of exercises if they stay within their RPE-phase. If training does not lead to worsening of symptoms for at least seven days and patients feel ready to, they can proceed to the next higher exhaustion phase ▪ In those cases, in which an adjustment of the training intensity should become necessary due to subjective exhaustion or Post-exertional Malaise, an adjustment of the extent and length is carried out according to the 5-phase model of the WHO recommendations [8]. That means we will return to a lower exhaustion phase
Closing session (Session 12)	▪ During the last session the subjects are offered to compare themselves with the games from the first session and to reflect on possible changes on a voluntary basis ▪ Short feedback is given and ways to improve the sustainability of the progress made are discussed

*RPE* subjective rate of perceived exhaustion*, WHO* World Health Organization*, PEM* Post-exertional malaise

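### Two sentences in the protocol conflict with its own patient masking, and would weaken it before a self-rated primary outcome if carried out as written

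*Protocol article*

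**What the plan says.** Under Masking and patient information, the patient side of the double-blind label rests on withholding. The section describes the approach as: "By also withholding information about the exact content of the interventions and the hypothesis of our study to patients". The leaflet and educational discussion present two new exercise programmes "without indicating that one of the programs is considered a control intervention". After randomisation patients learn about their own programme and "will not receive any information about the intervention in the other group".

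Later in the same section the protocol adds: "we will instruct patients before the post-intervention interview not to mention which group, control, or intervention, they belonged to". If unblinding happens during the assessment, the assessors are to document how and when.

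In the Comparison arm section, Table 2 gives this for Session 12: "During the last session the subjects are offered to compare themselves with the games from the first session". The same entry makes this step optional for the patient.

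The primary outcome is the change in FSS from T0 to T1, measured after a 72-hour resting state (Primary outcome). The FSS is patient-reported (Measures), and patient-reported outcomes are collected by electronic survey (Data collection). A sensitivity analysis leaving out unmasked patients is planned and stated twice (Statistical methods).

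**The concern.** A patient masked as planned does not know that either programme is a control. That patient therefore has no control-or-intervention label to keep back. An instruction phrased in those terms either presupposes an earlier disclosure that the leaflet policy rules out, or makes the disclosure itself.

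The Table 2 sentence raises a similar problem. Control patients have played no games, so the step cannot be delivered as written. The word also hints at what happens in the other arm, about which they are meant to hear nothing.

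What is at stake is the rating of the primary outcome. Blinded assessors do not protect a score that the patient gives; only the patient's own masking does. The section itself names expectancy and reporting bias as the reason for masking.

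**Working it through.** No figure in the plan depends on this point, so the check sets the texts side by side.

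**1. The control label.**
- Policy: the leaflet and discussion do not say that one programme is a control.
- Instruction before the post-intervention interview: do not say which group, naming control and intervention as the two options.
- Result: the two statements stand in the same section and conflict if the instruction is given in the words printed. The article offers no other wording for staff to use.

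**2. The games.**
- Table 2, opening sessions: each control session consists of two upper-body and two lower-body exercises chosen by the patient, such as biceps curls or wall presses. No game appears.
- Table 2, Session 12: refers to games from the first session.
- Table 1, Session 12 (VR arm): "the subjects are offered to compare themselves with the games from the first session". This is the same sentence, and there it fits the programme.
- Result: the control text looks carried over from Table 1. It conflicts with the control content and with the rule that patients hear nothing about the other arm.

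**3. Timing relative to the FSS.**
- Session 12 is the last training session, so for patients who complete training it precedes T1. The 72-hour resting state means it is not immediately before T1.
- The instruction precedes the post-intervention interview. The text does not say whether the T1 FSS survey is filled in before or after it. At baseline the questionnaire is sent before the in-person visit (Eligibility); nothing in the text says the same for T1.
- Both cues precede the self-reported FSS at three and six months, which are secondary outcomes.

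**4. Detection.**
- The sensitivity analysis needs a list of unmasked patients. The only stated source is the assessors' record of unblinding during the assessment.
- A patient who privately concludes that theirs was the control programme, and says nothing, may not appear in that record.

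**5. Reach.** If both sentences are carried out as written, the instruction concerns up to all 100 randomised patients and the Table 2 sentence up to the 50 controls.

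**6. Sample size.** The stated calculation is unaffected. A difference of 0.9, SD 1.5, two-sided 5% and 80% power give 44.6 per arm by the t-test, hence 45. Allowing for 10% dropout, 45 / 0.90 = 50 per arm.

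**The case against.** The strongest reply is that this is a matter of wording in a condensed article. Much of that stands, and it rules out several stronger readings that a reader might infer.

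- **That patients hear a fixed script.** The masking section is narrative and gives no verbatim text. The pair of labels may be the authors' gloss on the word *group*. The leaflets and session documentation are in additional files not shown here.
- **That control patients are made to compare games.** The comparison is offered and voluntary. A trainer whose patient did squats would be expected to refer to squats.
- **That the VR arm is revealed.** The word *games* discloses neither virtual reality, nor the flight device, nor the hypothesis. Patients already know that two programmes are compared and that they differ in technical implementation.
- **That the cues fall immediately before the rating.** The 72-hour rest separates Session 12 from T1, and the order of survey and instruction is not stated.
- **That the bias must favour VR by a definable share of the 0.9-point difference.** Learning that a control exists does not tell a patient which arm it is. Control trainers present their programme as first-line, and VR patients receive the same instruction. The documents give no basis for any size of shift.
- **That the effect would escape notice altogether.** A sensitivity analysis for unmasking is planned. Its stated source of information may miss private inference, which is a limitation rather than an absence.

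The two conflicts in the text remain. Calling one a gloss and the other a copying slip explains how they arose, but the protocol still states them as procedure, and neither agrees with its masking rules.

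**Conclusion.** The point holds in a limited form. Two sentences contradict the protocol's own patient masking and would weaken it if followed literally. Because the primary outcome is self-rated, this could affect reporting at T1, provided the cues are heard before the survey, and at follow-up. Neither the size nor the direction of any effect can be derived from the documents, and none is claimed.

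The conclusion assumes that staff work from the wording printed in the article. If the study materials already use neutral wording and the T1 FSS is already collected before the visit, only the article text needs correcting. The point is still worth acting on, because correcting it is nearly free and patient masking is the only protection the primary outcome has against expectancy.

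**What to change.** 1. Give the instruction before the post-intervention interview in neutral words, for example 'please do not describe the training you did', with no mention of control or intervention. Amend the masking section to match.
2. In Table 2, Session 12, replace *games* with *exercises*, and check the control-arm manual for the same carry-over.
3. State that the T1 FSS is completed before that instruction and before the assessor visit, keeping the 72-hour resting condition as it is.

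The cost is two wording changes and one stated order of procedures, with no added patients or visits and no change to the analysis. Recruitment was ongoing at submission (Trial status), so the change would help patients who had not yet reached Session 12 or T1.
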